### Setting

This study will be conducted at a private hospital in Qazvin, Iran. Qazvin is located near the equator at a latitude of 50° 36′ N.

### Inclusion and exclusion criteria

Inclusion criteria are as follows:
Nursing women with overweight (BMI 25–29.9 kg/m^2^) or obesity (BMI 30–39.9 kg/m^2^)Aged 20–49 years oldDelivered at term (gestational age of 37–42 weeks)Normal birth weight (2500–3900 kg)Declared exclusive nursing for the next 3 months

The exclusion criteria are:
PregnancyHaving gastrointestinal disorders interfering with bowel function, severe hepatic, renal (dialysis), inflammatory, cancer, diabetes, hypertension, epilepsy, and thyroid diseases, or taking any medicationRegular intake of vitamin D supplements or multivitamins (once or more per week)History of smoking or alcohol consumption once or more per week in the past monthAdhering to a specific diet during the past 3 months

### Randomization

This study is a double-blind, randomized, placebo-controlled, parallel trial. Subjects will be randomly assigned to three treatment groups using computer-generated codes. Randomization will be conducted by an assistant using permuted block randomization method and stratified randomization will be used to match the subjects based on age (20–34 and 35–49 years old) and BMI (25–29.9 and 30–39.9 kg/m^2^). Subjects will be randomly allocated into three groups of 2000 IU vitamin D/d (VD1), 4000 IU vitamin D/d (VD2), and placebo (P), and will be followed up for 12 weeks.

### Patient and public involvement statement

Patients and/or the public are not involved in the design, recruitment, and execution of the study. The main results will be disseminated to the subjects by email or telephone at the end of the study.

### Intervention

Vitamin D3 (as cholecalciferol) and placebo (as lactose) supplements are in the form of nano micro capsules and will be provided by the Nano Hayat Darou Industrial Co., Tehran. The capsules are identical in size, color, and shape. The present study will involve nursing mothers during autumn and winter. Ninety mothers who have just delivered will be invited to the study. Subjects will be randomly assigned to three groups to receive 2000 IU vitamin D/d, 4000 IU vitamin D/d, or placebo for 12 weeks. The length of intervention is selected based on similar clinical trials [30] and considering subject adherence.

Subjects will be required to consume one capsule with lunch and dinner. The intervention allocation will be blinded for both investigators and subjects. The double-dummy method will be used to double-blind the study. This means that the VD1 group will receive one capsule of vitamin D and one capsule of placebo per day. The VD2 group will receive two vitamin D capsules per day. Intervention will begin about 3 days after delivery and continue to 12 weeks later.

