**Methods/design:**

In a double-blind, randomized, placebo-controlled, parallel-group trial, after term delivery, 90 healthy women with overweight or obesity will be selected and randomly allocated into three groups to receive 2000 IU/d cholecalciferol (vitamin D3), 4000 IU/d cholecalciferol, or placebo (lactose) for 12 weeks while nursing. Measurements of height, weight, waist circumference, and body composition (fat mass (kg), lean mass (kg), body fat (%), fat mass index, and relative fat mass index) will be taken for all subjects at baseline and after 12 weeks of intervention. In addition, serum 25-hydroxyvitamin D (25(OH)D), parathyroid hormone, calcium, and phosphorus will be measured.

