The Institute of Medicine (IOM) recommended 600 IU vitamin D for nursing women, which is based on the role of vitamin D in bone health, but treating women with obesity may require more amounts of vitamin D. The Endocrine Society guidelines recommend that adults with obesity need two to three times more vitamin D (6000–10,000 IU/d) to treat and prevent vitamin D deficiency [19].

The results of a systematic review reported that findings on the effect of vitamin D supplementation on weight reduction in subjects with overweight and obesity were not conclusive [25]. However, most of the included studies in this review used a combined treatment of vitamin D and other substitutes, making interpretation of the findings more difficult. Another systematic review and meta-analysis reported that 25(OH)D levels are inversely correlated with body fat percentage (BFP), but no effect was found regarding vitamin D supplementation on BFP [26]. However, many included studies in this meta-analysis were not performed specifically in individuals with overweight or obesity and included postmenopausal women or patients with type 2 diabetes mellitus. In addition, some of these studies did not use high doses of vitamin D. On the other hand, a review study concluded that most clinical trials with null effect of vitamin D on health were performed in populations without vitamin D deficiency. So possible beneficial effects from vitamin D supplementation cannot be excluded [27].

To the best of our knowledge, the effect of different doses of vitamin D supplementation on anthropometric status and body composition has not been investigated specifically in nursing women with overweight or obesity. Only one study investigated the effect of vitamin D supplementation on body composition in nursing women with different weight statuses, including women with overweight or obesity. However, data for women with obesity has not been presented separately. Receiving 400 or 1200 IU/d of vitamin D for 6 months has not been found to influence body composition, which is probably due to the low amount of the vitamin. However, an inverse relationship has been reported between serum level of vitamin D and fat mass [28]. Therefore, further studies are needed to determine the appropriate amount of vitamin D for improving vitamin D status and body composition in nursing mothers with overweight or obesity. Thus, we proposed to start a randomized controlled trial with the following objectives:

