**Fig. 1 Fig1:**
[figure not shown]
Recruitment flow chart

Four types of questionnaires will be completed by each subject at the beginning and end of the study: socio demographic, 24-h recalls to collect dietary intake data, sunlight exposure questionnaire, and physical activity questionnaire (International Physical Activity Questionnaires (IPAQ)).

The necessary information on anthropometric measurements (height, weight, BMI, body fat percentage, body weight (kg), lean mass (kg), visceral fat, and visceral fat mass (kg), relative fat mass index (RFM), fat mass index (FMI) will be obtained using In Body model 270 as a body composition analyzer (In Body Co., Ltd, Seoul, Korea). Serum levels of vitamin D, PTH, as well as calcium and phosphorus levels will be measured at the beginning and end of intervention. Table 1 shows the primary and secondary outcome measures and the time for measurement and a Standard Protocol Items: Recommendations for Interventional Trials (SPIRIT) checklist is included as Additional file 1. The anthropometric and body composition measures, including height, weight, BMI, body fat percentage, body weight, lean mass, visceral fat and visceral fat mass, RFM, and FMI were intended to be primary outcomes but were unintentionally omitted in the preregistration. However, our sample size calculation is based on waist circumference as intended as a primary measure.

**Table 1 Tab1:** Outcome measures and measurement times

	Months	
	0	3
Primary outcomes		
Blood analysis		
Serum 25(OH)D	*	*
Serum PTH	*	*
Serum calcium	*	*
Serum phosphor	*	*
Anthropometry and clinical assessment		
Height (cm), weight (kg)	* *	*
Body mass index (kg/m^2^)	*	*
Waist circumference (cm)	*	*
Body composition		
Fat mass (kg)	*	*
Lean mass (kg)	*	*
Body fat (%)	*	*
Visceral fat mass (kg)	*	*
Fat mass index (FMI)	*	*
Relative fat mass index (RFM)	*	*
Secondary outcomes		
Weight (kg), height (cm), head circumference (cm), of the infants	*	*
Infection frequency in infants		*
Frequency of doctor visits		*

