### Sample size estimation

Sample size was calculated according to Roosta et al. [29] using two mean comparison formula. In this formula, considering α = 0.05, β = 0.2, and mean (standard deviation) of waist circumference changes after supplementation with vitamin D, which was equal to 1.91 cm (1.7) and 0.55 cm (1.04), respectively, in the intervention and control groups, sample size is estimated as 18 subjects. Since, there are three groups in this study, the calculated sample size was multiplied with $$ \sqrt{number\ of\ groups} $$, and finally the desired sample size for this study was obtained as 90 subjects (30 subjects per group).

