### Adherence and compliance

To assess the compliance of the subjects, they will be called every week. Subjects will receive supplements at the first visit and will be asked to bring all remaining ones for their last visit. Returned supplements will be counted to calculate the level of compliance and adherence to the intervention.

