### Statistical analysis

Missing data will be imputed using the regression imputation method. Quantitative variables will be reported as mean (standard deviation) and qualitative variables will be reported as percentages. ANOVA and Chi-square tests will be used to compare quantitative and qualitative variables in the three groups. To evaluate the effect of vitamin D supplementation on visceral fat mass, visceral fat percentage, lean mass, body fat percentage, waist circumference, FMI, RFM, BMI, and biochemical factors such as serum 25(OH)D, PTH, calcium and phosphorus levels two-way Repeated Measures ANOVA (RMA) will be applied in SPSS software version 21 (SPSS Inc., Chicago, USA). RMA assesses whether the mean changes in the results from baseline to 12 weeks differ in the three groups. This statistical analysis measures time to group interaction term. There are no planned interim analyses. The 95% confidence level will be considered.

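### The waist-change SD behind the sample size is not justified for a baseline taken about 3 days after delivery, and power for 1.36 cm drops below 80% once that SD exceeds about 1.85 cm

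*Protocol article*

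**What the plan says.** All references are to the protocol article.

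- **Timing.** Under Intervention: "Ninety mothers who have just delivered will be invited to the study", and then "Intervention will begin about 3 days after delivery and continue to 12 weeks later". Under Adherence and compliance: "Subjects will receive supplements at the first visit".
- **Measurement.** According to the Abstract (Methods/design), the anthropometric and body-composition measures "will be taken for all subjects at baseline and after 12 weeks of intervention". Table 1 lists them at months 0 and 3. No section names the postpartum day of the first measurement.
- **Sizing endpoint.** The text introducing Table 1 says that "our sample size calculation is based on waist circumference as intended as a primary measure".
- **Planning figures.** Sample size estimation takes from one cited study (reference 29) the "mean (standard deviation) of waist circumference changes after supplementation with vitamin D, which was equal to 1.91 cm (1.7) and 0.55 cm (1.04" cm), for intervention and control respectively, with α = 0.05 and β = 0.2. This gives 18, which is multiplied by the square root of the number of groups to reach 30 per group. The population of the cited study is not described.
- **Prior evidence.** The Background says the effect of different vitamin D doses on anthropometric status and body composition "has not been investigated specifically in nursing women with overweight or obesity". It identifies only one study of vitamin D and body composition in nursing women, which is reference 28.
- **Analysis.** "RMA assesses whether the mean changes in the results from baseline to 12 weeks differ in the three groups".
- **Attrition.** Strengths and limitations caps the total at 90 for financial reasons and takes 10% dropout as the maximum.

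**The concern.** If supplements are handed out at the first visit and started about 3 days after delivery, a pre-treatment baseline has to fall at about that day. The tape is placed midway between the iliac crest and the lower rib, so it crosses an abdomen that is still recovering from a term pregnancy. RFM is computed from waist, and fat mass, lean mass, body fat % and FMI come from impedance, so all of them share this baseline. Each woman's 12-week change is therefore postpartum recovery plus any treatment effect, and women recover by different amounts.

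The planning SD contains no visible allowance for that between-woman spread. It comes from reference 29, whereas the only study in nursing women that the Background identifies is reference 28. The protocol thus implies that the SD came from another population, and so from another kind of baseline. If the true SD is larger, a null waist result could reflect lack of precision while the stated planning figures make it look like adequate evidence of no effect.

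**Working it through.** **Inputs from the protocol.** Mean changes 1.91 and 0.55 cm; SDs 1.7 and 1.04 cm; α = 0.05 (taken as two-sided; sidedness is not stated); power 80%; 30 per arm; 10% dropout, so 0.9 × 30 = 27 per arm.

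**1. Reproducing the plan's figure.**
- Difference δ = 1.91 − 0.55 = 1.36 cm.
- Pooled SD = √[(1.7² + 1.04²)/2] = √[(2.890 + 1.082)/2] = 1.41 cm.
- Normal approximation: n = (1.960 + 0.842)² × (1.7² + 1.04²)/1.36² = 16.85, so 17 per group. The t-test version needs 18 (power 0.803), as stated.
- With the √3 factor: 17 × 1.732 = 29.4, or 18 × 1.732 = 31.2. The stated 30 is consistent with this to within 2 per group.

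The arithmetic is not at fault.

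**2. Does the mean matter?** If every arm's change shifts by a common amount c, then δ = (1.91 + c) − (0.55 + c) = 1.36 cm. For c = 0, 5, 10 or 15 cm, power at 30 per arm is the same (96%). Only the SD and δ count.

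**3. What the planned SD implies.** If changes are roughly normal, 95% of placebo women would change by 0.55 ± 1.96 × 1.04 cm, that is between −1.5 and +2.6 cm, from days after delivery to 12 weeks later. The Background itself says that milk production leads to gradual weight loss.

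**4. Power against the SD.** Two-sample t-test of one pairwise comparison, noncentrality δ/(SD × √(2/n)), two-sided 5%. The protocol gives no SD for change from day 3 postpartum, so 2 to 5 cm is an assumed range. The detectable difference is for 80% power: 0.736 × SD at 30 per arm and 0.777 × SD at 27.

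| SD of change (cm) | Power for 1.36 cm, 30/arm | Power, 27/arm | Detectable difference, 30/arm (cm) | Detectable difference, 27/arm (cm) |
|---|---|---|---|---|
| 1.41 (planned) | 96% | 94% | 1.04 | 1.09 |
| 2 | 74% | 69% | 1.5 | 1.6 |
| 3 | 41% | 37% | 2.2 | 2.3 |
| 4 | 25% | 23% | 2.9 | 3.1 |
| 5 | 18% | 17% | 3.7 | 3.9 |

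**5. Margin.** Power equals 80% at SD = 1.36/0.736 = 1.85 cm with 30 per arm, and at 1.36/0.777 = 1.75 cm with 27. If recovery adds an independent component to the planned spread, it uses up the margin when its own SD reaches √(1.85² − 1.41²) ≈ 1.2 cm. A component with SD 2 cm gives a total of √(1.41² + 2²) = 2.45 cm and 56% power at 30 per arm.

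**The case against.** The other side has several sound points.

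- **The contrast is unbiased.** There is a concurrent randomised placebo arm, and starting at delivery is consistent with the stated aim of informing postpartum care. A reader might infer that the early baseline biases the comparison, or that the 0.55 cm placebo mean undermines the sample size. Step 2 shows neither follows: a common shift of any size cancels.
- **The size of recovery is not in the document.** A reader might infer that the 12-week change is mainly uterine involution and fluid loss, or that the planning figures cannot describe this endpoint. The mechanism is plausible, but the protocol gives no magnitude and does not describe the population of reference 29. That the study was not in nursing women is inferred from the Background. What can be said is that the SD is not justified here.
- **The power loss is conditional.** The 80% belongs to 18 per group. The protocol's own inputs give 96% at 30, and there is slack up to an SD of about 1.85 cm.
- **No within-arm reading is planned.** The stated analysis is the time-by-group interaction, so the plan does not propose to treat falls within an arm as treatment effects.
- **Limitations are partly disclosed.** Sample size and non-gold-standard body composition are named. The immediate-postpartum baseline is not.

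These points narrow the finding but do not remove it. None of them supplies an SD suited to this baseline.

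**Conclusion.** The point holds in a limited form. The baseline is inferred, on good grounds, to be at about day 3 postpartum, and the SD that sizes the trial is evidently from a different setting. The contrast between arms remains valid; precision is what is exposed. An SD only about 0.44 cm above the planned 1.41 cm (0.34 cm with 10% dropout) takes power for 1.36 cm below 80%. Under assumed SDs of 2 to 5 cm, power at 30 per arm runs from 74% to 18%.

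These figures rest on a two-sided 5% test of one pairwise comparison, an unadjusted analysis of change, and an SD range that is an assumption. They do not show that the trial is underpowered; they show that the protocol gives no basis for saying it is adequately powered for waist.

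**What to change.** 1. In Sample size estimation, state that the SD was taken from a different population and baseline. In place of the implied power of 80% or more for 1.36 cm, give the pairwise difference detectable with 80% power from the table in the working: 1.5, 2.2, 2.9 and 3.7 cm at 30 per arm (1.6, 2.3, 3.1 and 3.9 cm at 27) for SDs of 2, 3, 4 and 5 cm.
2. State that a null waist result will be read against those figures.
3. In Statistical analysis, compare the 12-week value between arms with the measured day-3 value as covariate (ANCOVA). This uses data already collected and, apart from one degree of freedom, should be no less precise than analysing change, so the figures in item 1 stay on the cautious side. The gain cannot be quantified from the protocol. The measured baseline should not be replaced by pre-pregnancy BMI, which the protocol does not say is collected.

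**Cost.** Wording only, with no extra patients or visits. The drawback is that the stated power becomes less favourable.

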### Adherence and compliance

To assess the compliance of the subjects, they will be called every week. Subjects will receive supplements at the first visit and will be asked to bring all remaining ones for their last visit. Returned supplements will be counted to calculate the level of compliance and adherence to the intervention.

### Anthropometry and body composition

Body weight and height will be measured with subjects wearing minimal clothing and with bare feet. Weight will be measured to the nearest 0.1 kg using a calibrated digital weighing scale and height will be measured to the nearest 0.5 cm using a fixed stature meter (model number 26 SM). Waist circumference will be measured using a non-stretchable measuring tape from the point midway between the iliac crest and costal margin (lower rib) in the standing position. BMI will be calculated as weight in kilograms divided by the square of the height in meters. Bioelectrical impedance analysis (BIA) will be done using In Body model 270 as a body composition analyzer (In Body Co., Ltd, Seoul, Korea) to assess fat mass (kg), lean mass (kg), body fat (%), FMI as fat mass (kilogram) divided by the square of height (meters), and RFM calculated as:
$$ 76-\left(20\ \mathrm{height}\times \mathrm{waist}\ \mathrm{circumference}\ \mathrm{in}\ \mathrm{meters}\right) $$

BIA measurements are undertaken at least 6 h after breakfast. The subjects’ BIA measurements will be done while wearing light clothing and with bare feet and they will be asked to empty their bladders. The frequency used in this device is set as 20 and 100 kHz at each of the five body segments (right arm, left arm, trunk, right leg, left leg), and test duration is equal to 15 s.

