## Abstract

**Background:**

The optimal vitamin D intake for nursing mothers with overweight or obesity has not been defined. Vitamin D concentrations are associated with body composition indices, particularly body fat mass. Few studies have investigated the relationship between hypovitaminosis D, obesity, anthropometric status, and body composition in nursing women. Thus, the present study aims to investigate whether vitamin D supplementation during lactation will improve vitamin D status, reduce body fat mass, and improve body composition.

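### The printed relative fat mass (RFM) formula multiplies height by waist, so if used as written this primary outcome rises when the waist shrinks and an improvement reads as a worsening

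*Protocol article*

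**What the plan says.** The section Anthropometry and body composition introduces the index with "FMI as fat mass (kilogram) divided by the square of height (meters), and RFM calculated as" and then prints "76-\left(20\ \mathrm{height}\times \mathrm{waist}\ \mathrm{circumference}\ \mathrm{in}\ \mathrm{meters". The multiplication sign between height and waist is explicit, and the bracket encloses both. No other section gives a different formula.

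RFM is not a minor variable here:

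- Table 1 places it under primary outcomes, measured at months 0 and 3.
- The text before Table 1 says that "visceral fat and visceral fat mass, RFM, and FMI were intended to be primary outcomes but were unintentionally omitted in the preregistration".
- The Statistical analysis section names RFM among the variables tested by repeated-measures ANOVA, and explains that "RMA assesses whether the mean changes in the results from baseline to 12 weeks differ in the three groups".

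The Abstract sets the direction of benefit. The trial asks whether "vitamin D supplementation during lactation will improve vitamin D status, reduce body fat mass, and improve body composition".

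**The concern.** A fatness index that starts at a constant and subtracts a term can rise with waist only if the subtracted term falls as waist rises. A product of height and waist does the opposite, so the larger-waisted of two women of equal height is scored as less fat.

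Adult height is effectively constant over 12 weeks, so each woman's change in RFM is driven by her change in waist alone. Computed as printed, every waist reduction becomes an increase in RFM. If vitamin D reduced waist, the RFM result would point to harm and would contradict the waist measurement from which it is calculated.

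**Working it through.** The article reports no RFM value, so there is no figure to reproduce. The check is on the form of the formula.

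**Inputs**

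- Printed formula: RFM = 76 − 20·h·w, with h and w in metres (Anthropometry and body composition).
- Comparison form: RFM = 76 − 20·h/w. It keeps both printed constants and changes only the operator. It is an inference, because the article prints no alternative.
- Planning waist changes (Sample size estimation): "which was equal to 1.91 cm (1.7) and 0.55 cm (1.04), respectively, in the intervention and control groups". The sign is not printed; they are taken here as reductions (assumption).
- Heights of 1.50 to 1.70 m and waists of 0.80 to 1.10 m are illustrative assumptions.

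**Step 1: direction**

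- Printed: dRFM/dw = −20·h, negative at every height.
- Quotient: dRFM/dw = +20·h/w², positive at every height and waist.

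Both forms fall as height rises, so only the response to waist is at fault.

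**Step 2: women of the same height (h = 1.60 m)**

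| Waist (m) | As printed | Quotient |
|---|---|---|
| 0.80 | 76 − 20×1.60×0.80 = 50.4 | 76 − 32/0.80 = 36.0 |
| 0.95 | 76 − 20×1.60×0.95 = 45.6 | 76 − 32/0.95 = 42.3 |
| 1.10 | 76 − 20×1.60×1.10 = 40.8 | 76 − 32/1.10 = 46.9 |

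The ranking is reversed. Likewise, waists of 0.85 and 1.05 m score 48.8 and 42.4 as printed.

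**Step 3: change within one woman (h = 1.60 m, starting waist 0.95 m)**

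| Waist reduction | Change, as printed | Change, quotient |
|---|---|---|
| 2 cm (illustrative) | 46.24 − 45.60 = +0.64 | 41.59 − 42.32 = −0.72 (from unrounded values) |
| 1.91 cm (planning, intervention) | 20×1.60×0.0191 = +0.61 | −0.69 |
| 0.55 cm (planning, control) | 20×1.60×0.0055 = +0.18 | −0.20 |

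Over the full range of assumed heights and waists, a 1.91 cm reduction gives +0.57 to +0.65 as printed and −0.48 to −1.04 with the quotient.

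**Step 4: group contrast**

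A simulation of 4000 trials compared one active arm with control, 30 women each. It used the planning means and SDs for waist change, with assumed height 1.60 m (SD 0.06) and baseline waist 0.95 m (SD 0.08).

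| | As printed | Quotient |
|---|---|---|
| Mean difference in RFM change, active − control | +0.43 | −0.51 |
| Trials in which the difference favours active (lower RFM) | 0% | 100% |
| Trials significant at 0.05 (two-sample t test) | 96% | 96% |

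The printed form would therefore usually give a significant difference in the wrong direction.

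**Step 5: would a plausibility check catch it?**

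Over the assumed range, the printed formula gives values from 38.6 to 52.0. These look like believable body-fat percentages, so a range check on single values would not reveal the error.

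**The case against.** **It may be a misprint.** There is no operator between 20 and height, which suggests a misplaced symbol. A slip in an article does not prove that the trial will compute RFM this way. This stands as a limit: the formula is certainly wrong as printed, but inverted results are conditional on its use. It is, however, the only definition given to anyone deriving or checking the variable.

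**The values may come from another source.** The Study design text lists "relative fat mass index (RFM") among the measures obtained from the body composition analyser. Anthropometry and body composition instead gives a formula that needs waist, which that section measures by tape. The ambiguity is real and needs resolving, but it does not make the printed formula right.

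**The reach is limited.** Waist circumference, body fat percentage and FMI are analysed in their own right and do not use this formula. The sample size rests on waist. The time-by-group F test has no direction, so detection hardly changes. An RFM result moving against waist would also invite suspicion. All of this is true, and it confines the damage to the sign and size of the RFM means. Those are still the reported result for a listed primary outcome.

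**The quotient is not documented.** The article shows that the printed direction is wrong but does not show that the quotient is the only repair. This also stands. The quotient is the smallest change that keeps both constants and restores the direction, and the sponsor should confirm it.

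**Conclusion.** The concern holds. As printed, RFM falls by 20 × height for each metre of added waist (0.32 points per centimetre at 1.60 m), the opposite of what a fatness index must do. The reversal follows from the algebra and needs none of the assumed body sizes.

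The size does depend on assumptions. At 1.60 m, with the planning waist changes read as reductions, the active-minus-control difference in RFM change would be about +0.43 rather than about −0.51 points. The consequence for the results arises only if the formula is applied as printed. Because this is the operational definition of a listed primary outcome and the correction is trivial, it must be fixed before any RFM value is derived.

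**What to change.** - Replace the formula with RFM = 76 − 20 × (height / waist circumference), both in the same unit, after confirming it against the source of the index and citing that source.
- State that RFM is calculated from the stature-meter height and the tape-measured waist, and bring the Study design text, which attributes it to the analyser, into line.
- Check whatever spreadsheet or code derives RFM. A simple test is that, at a fixed height, a larger waist must give a larger RFM.
- If any values have already been computed from the printed line, recompute them.

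The cost is one line of text and a check of the derivation. Height and waist are already scheduled at both time points, so no new data are needed, and the sample size is unaffected.

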## Methods/design

### Study design

Subjects will be randomly assigned into groups with a 1:1:1 randomization ratio. A flow chart of the study protocol is presented in Fig. 1.

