### Blood sampling

Venous blood samples will be taken by the registered staff nurses between 9 and 10 am. The blood samples will be allowed to clot for about 60 min and will be centrifuged for 10 min at 2000 G within 2 h. All the blood serum will be stored at − 25 °C for further analysis. Blood serum will be used for analyzing calcium, phosphorus, PTH, and 25(OH)D3 levels, at baseline and the end of the study. Calcium and phosphorus levels will be measured by colorimetric enzymatic test (Pars Azmoon) and enzymatic photometric UV test BILT1500, respectively. For hormonal testing such as PTH, which need more precise testing, the Electrochemiluminescence (ECL) procedure, by Cobas e411 for Hitachi/Roche company, Germany, will be used. 25(OH)D3 will be measured by enzyme-linked immune sorbent assay (ELISA; Monobind Inc., Lake Forest, CA, USA).

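### The BIA timing rule counts from breakfast, not from the last food or drink, so it does not standardise feeding state between the two visits

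*Protocol article*

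**What the plan says.** In the protocol article, the section Anthropometry and body composition states: "BIA measurements are undertaken at least 6 h after breakfast". The remaining preparation rules there are that BIA is done "while wearing light clothing and with bare feet and they will be asked to empty their bladders". Neither that section nor any other mentions lunch, snacks or fluids before BIA, or sets an upper limit to the interval.

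Two other sections bear on the timing. Under Intervention, "Subjects will be required to consume one capsule with lunch and dinner". Under Blood sampling, "Venous blood samples will be taken by the registered staff nurses between 9 and 10 am".

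Table 1 lists fat mass, lean mass, body fat %, visceral fat mass and FMI as primary outcomes, each measured at months 0 and 3. Statistical analysis names all of these except fat mass in kg among the outcomes for repeated-measures ANOVA, with the time-by-group interaction as the effect of interest. The Discussion gives body composition as the main purpose of the trial.

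**The concern.** A minimum interval after a meal can only be meant to bring women to a comparable feeding state. Anchored to breakfast and open at the top, this rule does not do that. Six hours after an ordinary breakfast falls around midday or later, when another meal may well have been eaten. Two women can both comply, one having had nothing for six hours and the other having just finished lunch. The same woman can also be in one state at month 0 and in the other at month 3.

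With one measurement at each of two visits, there is nothing to average such differences out: error at either visit enters that woman's change in full. The cost is precision on outcomes the trial calls primary. Strengths and limitations says that the sample is capped at 90 for financial reasons, so lost precision cannot be bought back with more women.

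**Working it through.** **1. What the rule permits.** Assume breakfast at 7 to 8 am (the article gives no mealtimes). The earliest permitted BIA is then 1 to 2 pm. A woman with breakfast at 8 am, lunch at 1:30 pm and BIA at 2:30 pm is measured 6.5 h after breakfast and 1 h after a meal. She meets every stated condition. The example is constructed; it shows what the text allows, not what the site will do.

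**2. Whether another section closes the gap.** The 9 to 10 am slot applies to blood only. A BIA in that slot, 6 h after that day's breakfast, would need breakfast at 3 to 4 am, so the blood-draw time does not control BIA timing. The capsule instruction shows that lunch is an expected meal during treatment, but it says nothing about the order of lunch and BIA. The clothing and bladder rules do not concern intake. Nothing closes the gap.

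**3. Size in one woman at one visit (assumed values).** Take a weight of 75 kg, a fat mass of 30 kg, and intake *g* of 0.5 to 1.0 kg counted wholly as fat. Body fat % = 100 × (30 + *g*)/(75 + *g*).

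- *g* = 0: 30/75 = 40.0%
- *g* = 0.5: 30.5/75.5 = 40.4%
- *g* = 1.0: 31/76 = 40.8%

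The reading is therefore 0.4 to 0.8 percentage points too high, and fat mass 0.5 to 1.0 kg too high, at that visit.

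**4. Size for the group comparison (assumed values).** With two time points, the time-by-group test compares mean changes. Let *s* be the SD of fat-mass change without feeding error and *v* the SD of the error at each visit, independent between visits and of the true change. Then

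variance of change = *s*² + 2*v*², so the inflation is 1 + 2*v*²/*s*².

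As a benchmark, take a two-arm comparison with 30 per arm that has 80% power at two-sided 0.05 without the error. Its power becomes Φ(2.80/√inflation − 1.96).

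| *s* (kg) | *v* (kg) | Inflation | Power |
|---|---|---|---|
| 3.0 | 0.3 | 1 + 0.18/9 = 1.02 | 79% |
| 2.0 | 0.5 | 1 + 0.50/4 = 1.125 | 75% |
| 1.5 | 0.7 | 1 + 0.98/2.25 = 1.44 | 65% |

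The article gives neither *s* nor *v*. If the errors at a woman's two visits have correlation ρ, the added term is 2*v*²(1 − ρ). That is why the same feeding state and time of day at both visits would help even if some error remains.

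**5. The plan's own figure.** The article gives no figure for BIA error. Its sample size rests on waist circumference: "considering α = 0.05, β = 0.2", with changes "which was equal to 1.91 cm (1.7) and 0.55 cm (1.04), respectively, in the intervention and control groups". (1.96 + 0.84)² × (1.7² + 1.04²)/(1.91 − 0.55)² = 16.85, so 17 per group. An exact *t* calculation gives 18 (power 80.3%), as stated. Waist is measured by tape, so this calculation does not depend on the BIA rule.

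**The case against.** The strongest reply is that a six-hour interval after breakfast makes sense only if breakfast is the last intake, so this is loose wording in a condensed article and not a poor design choice. That intention is plausible. But the text does not state it, and the article gives the operative rule instead of leaving it to a manual; a site that follows it literally need not exclude lunch. If breakfast was meant as the last intake, saying so would close most of the gap.

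Several further objections stand and limit the point:

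- **Lunch is not compulsory before BIA.** A reader might infer that it is, because a capsule goes with it. The instruction governs capsules during treatment. It does not apply to a baseline taken before capsules begin, and it is only weak support at month 3.
- **Counting intake as fat is an assumption.** The article does not describe the device's algorithm. It says that impedance is taken at five segments including the trunk, and absorbed fluid could itself alter the reading.
- **A gap of 1 to 2 kg between two women is a worst case.** It needs opposite feeding patterns (2 × 0.5 to 2 × 1.0 kg) and complete misassignment to fat.
- **The separate blood-draw time is not a defect.** No analysis requires the two measurements to coincide.
- **Not every outcome is touched.** RFM is calculated from height and waist, and waist is not a BIA reading.

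The article already concedes that body composition is not measured by a gold-standard technique. That limitation does not name feeding state, which one sentence could control.

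**Conclusion.** The point holds as a cheap improvement in precision. The stated rule does not standardise feeding state, within or between visits, for BIA outcomes listed as primary.

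A reader might go further and infer a biased treatment effect. The documents do not support that: allocation is randomised and blinded, so feeding error should be similar in the three arms. It adds noise to each woman's change and lowers power; it does not by itself shift the difference between arms.

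The size is uncertain. On the assumptions shown, one visit's body fat reading could be off by 0.4 to 0.8 percentage points. Power that would otherwise be 80% falls to somewhere between 79%, which is negligible, and 65%, which is not. All of this rests on assumed intake, assumed SDs and full assignment of intake to fat; the true effect may be smaller or run in the other direction. The finding about the text needs none of these assumptions.

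**What to change.** In Anthropometry and body composition, replace the breakfast rule with one that:

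- counts the interval from the last food or drink;
- requires BIA at the same time of day at month 0 and month 3; and
- has the time since last intake recorded at each visit.

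One convenient way to meet this is a morning measurement before breakfast at the blood-draw visit, but sharing the visit is not essential. Waist measurement need not move, and nothing in the documents supports a rule on time since nursing.

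The cost is one amended sentence and one recorded time per visit. The drawback is that a nursing mother waits to eat before two measurements.
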